## Abstract

**Background:**

The primary treatment for schizophrenia currently relies on medication. Nevertheless, the efficacy of medication for Cognitive Impairment Associated with Schizophrenia (CIAS) is constrained, and it is also accompanied by side effects. Consequently, the investigation of novel non-pharmacological strategies is essential. High-definition transcranial direct current stimulation (HD-tDCS) and aerobic exercise (AE) have emerged as promising approaches for cognitive enhancement in individuals with schizophrenia. This study aims to evaluate the efficacy of integrating HD-tDCS with AE for CIAS and to elucidate the underlying mechanisms of this synergistic intervention.

**Methods:**

A randomized, double-blind, controlled trial will be conducted. The CIAS will be randomly allocated to one of four groups: MRI-guided HD-tDCS + AE, MRI-guided HD-tDCS alone, AE alone, and a control group. Structural magnetic resonance imaging (MRI) data will be obtained to determine the optimal electrode placement. The central electrode will be positioned over the medial prefrontal cortex (mPFC). Both HD-tDCS and AE will be administered five times per week over a four-week period, resulting in a total of 20 sessions. The primary outcome measure will be the change in cognitive function, evaluated using the MATRICS Consensus Cognitive Battery. Secondary outcomes will include changes assessed by the Repeatable Battery for the Assessment of Neuropsychological Status and the Wisconsin Card Sorting Test which are designed to evaluate global and executive functions. The Facial Emotion Perception Test and the Voice Emotion Perception Test will be utilized to assess social cognition. The severity of clinical symptoms will be quantified through the Positive and Negative Syndrome Scale and the Brief Psychiatric Rating Scale. This study will incorporate functional near-infrared spectroscopy, MRI, electroencephalography, P300 event-related potential, eye movement examination and plasma brain-derived neurotrophic factor (BDNF) levels to investigate the underlying mechanisms. Assessments will be evaluated at baseline (T0), after 2 weeks (T1), after 4 weeks (T2), and after 6 months (T3).

**Discussion:**

The integration of MRI-guided HD-tDCS targeting the mPFC and AE presents an efficacious and individualized treatment strategy for CIAS. This proof-of-concept study may provide a multi-dimensional view of biological mechanisms underlying HD-tDCS combined with AE in precision psychiatry.

**Trial registration details:**

The study is registered with https://www.chictr.org.cn/ protocol registration number ChiCTR2500106980 (date of registration: 1. August. 2025). It was approved by the Research Ethics Committee of the Second Affiliated Hospital of Xinxiang Medical University (Approval Code: XYEFYLL-2025-16, Approval Date: 17 February 2025). Recruitment began in December 2025.

## Background

Cognitive Impairment Associated with Schizophrenia (CIAS) is a core symptom of schizophrenia, and its severity directly affects patients’ social functioning, activities of daily living, and long-term prognosis (1, 2). The extent of cognitive function improvement is a key prognostic indicator for patients with schizophrenia (3). Current antipsychotic medications primarily target the dopamine system and effectively alleviate positive symptoms but have limited impact for CIAS (4). Cognitive abilities of individuals with schizophrenia do not necessarily enhance with the remission of psychotic symptoms (5, 6). Although several potential cognitive-enhancing agents have advanced to Phase III trials as adjuncts to antipsychotic treatment, none have yet demonstrated sufficient efficacy to secure FDA approval for schizophrenia (7). Furthermore, variability in individual responses and adherence to therapy pose additional challenges (8). Consequently, the exploration of novel non-pharmacological strategies is critically important.

High-definition transcranial direct current stimulation (HD-tDCS) is a non-invasive intervention technique that utilizes a constant direct current to modulate cortical neuron activity. Compared to conventional tDCS, HD-tDCS provides more precise cortical stimulation targeting, enhanced cortical penetration, and the potential for targeted neuromodulation, which can lead to specific symptomatic changes (9, 10). Multiple randomized controlled trials have indicated that tDCS targeting regions such as the prefrontal cortex significantly enhances working memory and executive functions in patients (11, 12). Research has demonstrated that HD-tDCS can improve the integrity of specific white matter tracts in individuals with chronic schizophrenia, which is associated with enhanced attentional function (13). A recent meta-analysis further substantiates that HD-tDCS exerts a moderate effect on overall cognitive function in schizophrenia (14). Mechanistically, HD-tDCS may enhance cognition by modulating cortical neuronal excitability, promoting synaptic plasticity, and influencing associated neurotransmitter systems (15). Overall, HD-tDCS exhibits clear potential and value for CIAS. Concerning the selection of stimulation sites, previous studies have demonstrated that cognitive impairments, such as deficits in episodic and working memory and challenges in emotional regulation, are associated with dysfunction in the medial prefrontal cortex (mPFC) and altered connectivity with subcortical regions (16). Furthermore, dysregulation of dopaminergic activity in the mPFC is associated with the progression of schizophrenia (17, 18). Delayed dopamine release in the medial prefrontal cortex (mPFC) is a defining characteristic of the pathophysiology of schizophrenia (19). A deficiency in the dopamine transporter leads to reduced spine density in mPFC pyramidal neurons, resulting in mPFC dysfunction and potentially contributing to behavioral abnormalities in schizophrenia. The primary manifestations are abnormalities in attention (e.g., poor concentration), memory (especially working memory), and executive functions (e.g., deficits in planning, decision-making, and cognitive flexibility) (20). Postmortem studies and schizophrenia mouse models, induced by neonatal basolateral amygdala lesions, also demonstrate reduced dendritic spine density in mPFC pyramidal neurons (21, 22). Consequently, the mPFC has been selected as the target in this study. Research utilizing HD-tDCS targeting the mPFC in schizophrenia remain limited. Further, individual anatomical variations can substantially affect the outcomes of HD-tDCS altering the distribution of electrical currents within the cortical regions, thereby impacting therapeutic efficacy (23, 24). The use of MRI-guided HD-tDCS interventions enables the identification of optimal electrode placements tailored to each individual, thereby reducing the impact of structural brain differences and enhancing the effectiveness of HD-tDCS (25, 26). Consequently, this study will utilize MRI to obtain anatomical data for each participant, and develop appropriate therapeutic target for individualized precision therapy for CIAS.

Aerobic exercise (AE) is one of the psychosocial interventions with most robust evidence for CIAS (27). AE exerts its effects through multiple mechanisms. It has been demonstrated to influence brain neuroplasticity via neurogenesis and structural alterations (28, 29). Furthermore, AE can mitigate age-related cognitive decline by altering brain metabolism, structure, and connectivity (30). Additionally, AE significantly enhances the activity of mPFC and improves cognitive function within this region (31, 32). Accumulating evidence suggests that structured AE programs can lead to improvements in executive function, attention, and memory in patients with schizophrenia, possibly through mechanisms involving enhanced prefrontal oxygenation and neurotrophic support (33). HD-tDCS has demonstrated promising results in disease intervention, recent studies indicate that its therapeutic effects may be further enhanced when combined with AE intervention methods (34, 35). Consequently, this research aims to examine the synergistic effects of combined HD-tDCS with AE for CIAS.

This study employed a simultaneous intervention approach utilizing HD-tDCS and AE, based on the evidence of the temporal effect of combined intervention. A comprehensive review suggests that integrating neuroregulation with psychosocial methods yields superior outcomes in enhancing cognitive function and alleviating negative symptoms in individuals with schizophrenia, compared to singular interventions; it also highlights the critical role of intervention timing in determining efficacy (36). Furthermore, a randomized controlled trial further confirmed that the concurrent application of neuroregulation and psychosocial strategies significantly ameliorates cognitive deficits and negative symptoms in schizophrenia patients (37). Consequently, the synchronous research design is underpinned by a sound theoretical and empirical rationale. In terms of the therapeutic mechanism, HD-tDCS and AE may exert their effects through a multi-level synergies: AE enhances the secretion of brain-derived neurotrophic factor (BDNF), thereby promoting synaptic plasticity (38, 39), BDNF is not only a key factor for the survival and functional maintenance of neurons, but also regulates synaptic structure and function, especially in the prefrontal cortex, where it supports the long-term potentiation effect, which is the neural basis for learning and memory formation (40). HD-tDCS can regulate the excitability of cortical neurons through direct current, and it supports the neuroplastic mechanism mediated by BDNF, thereby forming a bidirectional synergistic enhancement effect (41). Secondly, AE improves the blood flow to the brain, reduces oxidative stress responses, and enhances mitochondrial function and metabolic efficiency, thereby providing a more favorable physiological environment for the brain (42). Concurrently, HD-tDCS directly modulates the excitability of the mPFC, enhancing the metabolic improvement such as reduced oxidative stress and increased cerebral blood flow induced by AE, thus facilitating cognitive enhancement (43). The combination of the two can promote the increase of blood flow and oxygenation levels in the mPFC area, thereby enhancing its role in executive functions, working memory, and emotional processing. Exploring this integrated intervention approach could offer a novel and effective intervention option for CIAS.

This study aims to investigate three principal aspects. The primary objective of this study is to evaluate the efficacy of the combined intervention of HD-tDCS and AE in enhancing cognitive function at the individual level. Additionally, we aim to assess the long-term impact of this intervention over a six-month period, focusing on changes in cognitive function, clinical symptoms-measured by the Positive and Negative Syndrome Scale (PANSS) and Brief Psychiatric Rating Scale (BPRS), social function-measured by Social Disability Screening Schedule (SDSS), and Schizophrenia Quality of Life Scale (SQLS). Furthermore, the study seeks to elucidate the biological mechanisms of MRI-guided HD-tDCS and AE from a multi-dimensional perspective. By evaluating the feasibility and safety of this precision approach, the study aims to provide biological insights into individualized treatment strategies for CIAS.

## Methods

### Study design

This randomized, double-blind, controlled clinical trial evaluates the efficacy of combining HD-tDCS with AE to improve cognitive function in individuals with CIAS. Eligible participants will be randomly assigned to one of four groups in equal proportions (1:1:1:1): MRI-guided HD-tDCS +AE (Group 1), MRI-guided HD-tDCS alone (Group 2), AE alone (Group 3), and a control group (Group 4). Assessments will be conducted at baseline (T0), at 2 weeks (T1), at 4 weeks (T2), and at 6 months post-intervention (T3). The specific intervention measures for each group are delineated as follows: the MRI-guided HD-tDCS + AE group first undertakes a 15-minute warm-up exercise. Subsequently, HD-tDCS and AE treatments are administered concurrently for a duration of 30 minutes. The HD-tDCS group receives 30 minutes of electrical stimulation per session. The AE group’s intervention comprises a 15-minute warm-up followed by a 30-minute formal AE stage, amounting to a total of 45 minutes. The control group does not receive HD-tDCS or AE but instead is provided with routine psychiatric care, including regular psychiatric follow-ups, medication management, and general health guidance, but no experimental interventions. Each intervention for the aforementioned groups is conducted once daily, five days a week, over a period of four weeks, culminating in a total of 20 sessions. The study design is illustrated in **Figure 1**.

**Figure 1 f1:**
[figure not shown]
Flowchart of the study design.

### Recruitment

Participants will be recruited from the Department of Psychiatry at the Second Affiliated Hospital of Xinxiang Medical University. The trial will be publicized via the hospital’s official website and various media outlets. Information leaflets will be distributed within the Department of Psychiatry, where psychiatrists will provide an overview of the study. Potential participants will receive both oral and written information regarding the research procedures, along with their potential benefits and risks. All participants and their legal guardians, will sign informed consent forms. In accordance with the Helsinki Declaration on Ethical Principles for Medical Research Involving Human Subjects, this study received approval from the Research Ethics Committee of the Second Affiliated Hospital of Xinxiang Medical University (Approval Number: XYEFYLL-2025-16, Approval Date: February 17, 2025) and has been registered with the Chinese Clinical Trial Center (Registration Number: ChiCTR250010698). The trial will take place at the Second Affiliated Hospital of Xinxiang Medical University. This research protocol adheres to the 2013 Standard Protocol Items: Recommendations for Intervention Trials (SPIRIT) Statement Guidelines (44).

### Eligibility criteria

Eligible individuals must meet the following inclusion criteria (1): The current episode of the patient aligns with the diagnostic criteria for schizophrenia according to the Diagnostic and Statistical Manual of Mental Disorders-5 (DSM-5) (2). patients who achieved the stable period through oral antipsychotic drug treatment, as judged by the following criteria: delusion, hallucinatory behaviors, exaggeration, and suspicion/victimization items in the positive and negative symptom scale (PANSS), abnormal thought content scores of ≤ 5 in the general psychopathology scale, and PANSS conceptual disorganization scores of ≤ 4, if all the aforementioned criteria were met, the patient was considered to be in a stable period of schizophrenia (45) (3). Patient must be undergoing treatment with atypical antipsychotic medications, with equivalent doses calculated using the defined daily dose method (4). To minimize study population heterogeneity only Han ethnic participants will be enrolled (5). Aged between 18 and 55 years (6). Written informed consent must be obtained from the patient. Exclusion criteria (1): Individuals with organic brain lesions, intellectual disabilities, or other physical ailments (2). Those experiencing intracranial hypertension (3). Frequent or persistent migraines (4). Individuals with a personal history of epilepsy or a familial history of epilepsy (5). Patients possessing metallic implants within their bodies (6). Severe substance uses disorder (7). Pregnant women or those who are breastfeeding (8). Subjects currently displaying significant abnormalities in laboratory tests (i.e. blood routine, liver and kidney function, electrolytes, and thyroid function. Results that exceed the normal range and are recognized by the attending psychiatrist as having clinical significance, such as severe anemia, acute liver/kidney function disorders) (9). Patients undergoing modified electroconvulsive therapy (10). Individuals with a history of limb disability or leg injury. Participants will be evaluated based on the inclusion and exclusion criteria outlined in **Table 1**.

**Table 1 T1:** World Health Organization trial registration data set related to this study.

Data category	Information
Primary Registry and Trial Identifying Number	ChiCTR2500106980
Date of Registration in Primary Registry	1. August. 2025
Secondary Identifying Numbers	N/A

Key Inclusion and Exclusion Criteria	Inclusion criteria: 1. The current episode of the patient aligns with the diagnostic criteria for schizophrenia according to the Diagnostic and Statistical Manual of Mental Disorders-5 (DSM-5). 2. patients who achieved the stable period through oral antipsychotic drug treatment, as judged by the following criteria: delusion, hallucinatory behaviors, exaggeration, and suspicion/victimization items in the positive and negative symptom scale (PANSS), abnormal thought content scores of ≤ 5 in the general psychopathology scale, and PANSS conceptual disorganization scores of ≤ 4, if all the aforementioned criteria were met, the patient was considered to be in a stable period of schizophrenia (45). 3. Patient must be undergoing treatment with atypical antipsychotic medications, with equivalent doses calculated using the defined daily dose method. 4. To minimize study population heterogeneity only Han ethnic participants will be enrolled. 5. Aged between 18 and 55 years. 6. Written informed consent must be obtained from the patient. Exclusion criteria: 1. Individuals with organic brain lesions, intellectual disabilities, or other physical ailments. 2. Those experiencing intracranial hypertension. 3. Frequent or persistent migraines. 4. Individuals with a personal history of epilepsy or a familial history of epilepsy. 5. Patients possessing metallic implants within their bodies. 6. Severe substance uses disorder. 7. Pregnant women or those who are breastfeeding. 8. Subjects currently displaying significant abnormalities in laboratory tests (i.e. blood routine, liver and kidney function, electrolytes, and thyroid function. Results that exceed the normal range and are recognized by the attending psychiatrist as having clinical significance, such as severe anemia, acute liver/kidney function disorders). 9. Patients undergoing modified electroconvulsive therapy. 10. Individuals with a history of limb disability or leg injury.
Study Type	Interventional Allocation: randomized Masked: double blind Primary purpose: schizophrenia intervention
Date of First Enrollment	December 2025
Sample Size	48
Recruitment Status	Pending
Primary Outcome(s)	Changes in The Chinese version of the MATRICS Consensus Cognitive Battery (MCCB)
Key Secondary Outcomes	Changes in Repeatable Battery for the Assessment of Neuropsychological Status (RBANS), Wisconsin Card Sorting Test (WCST), Facial Emotion Perception Test (FEPT), the Voice Emotion Perception Test (VEPT), Brief Psychiatric Rating Scale (BPRS), Positive and Negative Syndrome Scale (PANSS), Social Disability Screening Schedule (SDSS) and the Schizophrenia Quality of Life Scale (SQLS)
Ethics Review	Approved (Approval Number: XYEFYLL-2025-16) Approval Date: 17 February 2025 The Second Affiliated Hospital of Xinxiang Medical University, [contact], [name]
Completion date	Pending
Summary Results	Pending
IPD sharing statement	N/A

### Randomization

The randomization process will be conducted by an independent researcher who is not involved in the experiment. This researcher will utilize a random number table to randomly allocate participants into four distinct groups, labeled as “1, 2, 3, and 4.”. Specifically, the group coding is as follows: Group 1 corresponds to the HD-tDCS combined with AE group, Group 2 to the HD-tDCS group, Group 3 to the AE group, and Group 4 to the control group. The random allocation process will be implemented using Microsoft Excel 2019. Upon the recruitment of all 48 eligible participants, each individual will be assigned a unique identifier and paired with a randomly generated value using Excel’s “=RAND ()” function. The “Paste Special” function will then be employed to convert these random numbers into fixed values. Subsequently, the list of participants will be sorted in descending order based on the random values, with participants allocated to groups 1 to 4, each comprising 12 individuals, according to their ranking positions. Once the randomization scheme is established, it will be sealed within an opaque envelope, which will be opened sequentially in accordance with the order of subject enrolment. The allocation scheme contained within each envelope will dictate the group assignment for the corresponding participant. This approach ensures that researchers are unable to access the randomization scheme in advance, thereby safeguarding the integrity of the randomization process.

### Blinding

All participants and researchers will remain blinded throughout the research process. During the entire research process, the designated stimulus conditions will be kept strictly confidential and will only be disclosed to the principal researcher. Four distinct groups will be tasked with administering the treatment, with strict measures in place to prevent inter-group communication regarding the particulars of each treatment. Each group will be informed only of its own treatment protocol and will remain unaware of the grouping details or the treatment plans of the other groups. The principal investigator will assign specific measures to each group, which will then implement the experimental treatment for their respective patient cohorts. Patients will remain unaware of their group allocation and will be instructed not to discuss the grouping, the treatment received, the completion of questionnaires, or any other aspects of the experimental protocol. During the phase of result measurement, personnel involved in data collection and analysis will also be blinded to the grouping information and specific measures. Subsequently, the principal investigator will conduct two unblinding procedures: the first will occur before data locking, and the second will follow data analysis. The initial unblinding will occur after data locking, organizing the data into groups 1–4 without disclosing the actual correspondence between these groups and their respective identities. The second unblinding will take place after the data analysis, explicitly revealing the specific identities of groups 1-4. Furthermore, to ensure that participants are unaware of their group assignments, the intervention activities will be conducted in designated rooms. Although the researchers will be aware of the group assignments, they must not disclose this information to the participants and will not be involved in the evaluation or analysis of the study. Additionally, the evaluators and data analysts will remain unaware of the intervention group’s situation throughout the entire research process.

All researchers involved in data management and statistical analysis will remain blinded to the grouping information throughout the entire process. Specifically, data will be analyzed using coded group identifiers (e.g., Group A, B, and C), and the blinding code will remain undisclosed until the completion of the statistical analysis and the locking of the database. This procedure aligns with the principle of the blind method for minimizing assessment bias, as outlined in clinical trial protocols (46).

A Blinding Integrity (BI) assessment will be conducted following the final intervention session. Participants will be required to specify their perceived group allocation via a forced-choice questionnaire, asking: “Which intervention do you believe you received?” The response options will include (1): Combined HD-tDCS and AE (2), HD-tDCS alone (3), AE alone (4), Control, or (5) Unsure. To rigorously assess the blinding effect, Bang’s Blinding Index (BI) will be calculated for each group. This index allows for the distinction between genuine unblinding and random guessing. The BI is the primary tool for quantitatively evaluating the effectiveness of blinding implementation in clinical trials. By calculating the BI separately for each group, we can accurately assess the maintenance of blinding across different intervention groups (47).

Unlike drug trials, these trials—such as those involving surgery, rehabilitation, psychological, and physical therapy—cannot physically blind the “treatment itself” (48). During the informed consent process, we informed participants that the study was designed to investigate the effects of non-pharmacological interventions on cognitive function of individuals with schizophrenia. In the informed consent form, all intervention measures were described as “interventions with potential benefits,” without disclosing which group was the experimental group and which was the control group.The language used in the informed consent form was intentionally general to avoid revealing specific differences between groups, thereby minimizing the expectancy effect. Upon completion of the study, it is imperative to fully disclose the actual research design and the group assignments to all participants.

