### Date management

The evaluation of cognitive function and the severity of psychiatric symptoms will be conducted by two psychiatrists, who will remain blinded to the group assignments. All demographic information and scale-related data will be recorded in electronic Case Report Forms (eCRFs) and stored on a designated website. Access to the securely stored eCRFs will be restricted to the project leader and the principal investigator. To maintain confidentiality, anonymization will be implemented during data entry by substituting patients’ actual names with unique identification numbers. The independent data monitoring committee will be established to monitor safety, the occurrence of adverse events, and advise on trial design decisions.

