This study presents some limitations. Firstly, the lack of a “sham” exercise or “sham” HD-tDCS compromises the complete blinding of participants, which may enhance the “expectancy effect” within the combined group. Although this study primarily investigates the synergistic feasibility of the two active interventions, future research should incorporate Sham-tDCS and an Active Control condition (such as stretching or low-intensity tasks) to balance “attention time” and “treatment expectation” across all participant groups. Secondly, cognitive tasks during treatment were not included in this study. Future research should incorporate cognitive tasks (such as N-back) concurrently with the intervention measures to enhance the magnitude and specificity of cognitive improvement. Thirdly, the sample size is relatively small, potentially compromising statistical power. Fourthly, the study lacks an analysis of various parameters of AE, Consequently, future research should focus on enlarging the sample size, and investigating optimal AE parameters. Fifthly, this study is the single center design, which may have a center effect and a selection bias. Further larger, prospective, multicenter studies are worthwhile.

This randomized, double-blind, controlled clinical design incorporated a multi-dimensional assessment will provide biological insights for the synergistic effect of HD-tDCS and AE on cognitive improvement. The integration of MRI-guided HD-tDCS targeting the mPFC with AE constitutes a promising avenue for cognitive rehabilitation in schizophrenia. This approach holds significant translational and clinical potential in precision psychiatry. Implementing these individualized therapeutic strategies may yield substantial clinical and economic benefits in the management of CIAS.

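### The trial is labelled double-blind, but the text supports at most blinding of outcome assessors and analysts, and the unblinding order and group codes that should protect the analysts contradict each other

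*Protocol article*

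**What the plan says.** The double-blind label appears in the Abstract, Study design, Table 1, the caption of Figure 2, and several times in the Discussion. The Blinding section opens with "All participants and researchers will remain blinded throughout the research process".

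Elsewhere the article says:

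- **Arms.** Study design gives Group 1 stimulation during cycling, Group 2 stimulation, Group 3 cycling, and Group 4 routine psychiatric care with no experimental procedure. No sham is described.
- **Masking of treatment.** The Blinding section accepts that in trials of physical or rehabilitative treatment the treatment itself cannot be physically masked. The first limitation in the Discussion is that the absence of sham exercise or sham "HD-tDCS compromises the complete blinding of participants".
- **Researchers.** Later in the Blinding section: "Although the researchers will be aware of the group assignments". They are to keep this from participants and take no part in evaluation or analysis. Evaluators and analysts are to stay unaware.
- **Order of unblinding.** Of the two planned unblindings, "the first will occur before data locking, and the second will follow data analysis". The next sentence reads: "The initial unblinding will occur after data locking".
- **Codes.** At the first unblinding the data are arranged as groups 1 to 4 with identities withheld. The Randomization section has already defined those numbers, for example "Group 1 corresponds to the HD-tDCS combined with AE group". The next part of the Blinding section describes letter codes instead, kept closed until analysis and lock are complete.
- **Check on blinding.** Patients choose among the four arms or Unsure, and Bang's index is computed per arm. The article says: "This index allows for the distinction between genuine unblinding and random guessing".

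**The concern.** Readers take a double-blind label to mean that patients' expectations cannot differ between arms. Here patients can see whether they cycled or wore electrodes, and staff can see what they delivered. Every contrast with control therefore combines the intervention with expectancy and contact time. This matters most for outcomes that rest on the patient's own report. The Outcomes section describes the quality-of-life scale (SQLS) as reflecting subjective experience.

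Without patient and staff blinding, protection against bias rests on the assessors, the analysts and the order of lock and unblinding. The article gives two positions for the first unblinding and two coding schemes. One of those schemes uses labels that the article itself decodes.

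The blinding check is a smaller matter. If its null value is misplaced, an arm in which patients identify their treatment well above chance can be read as well blinded.

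**Working it through.** The article gives no figure on this point to reproduce. The first three steps compare statements; the last two are arithmetic.

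**1. Who is blinded.**

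| Role | Claimed | What the rest of the text supports |
|---|---|---|
| Participants | Blinded throughout | Arms differ visibly, no sham, masking conceded to be incomplete |
| Treating researchers | Blinded throughout | Aware of the assignments |
| Outcome assessors | Blinded | Nothing in the text contradicts this |
| Analysts | Blinded | Holds only if the codes are neutral |

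**2. Order of unblinding.** One sentence puts the first unblinding before data lock, and the next puts it after. Both cannot be true. The later paragraph keeps the code closed until analysis and lock are both complete, which is compatible only with the after-lock version if the first unblinding reveals anything about the arms.

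**3. Codes.** Study design and Randomization both fix 1 as the combination, 2 as stimulation, 3 as exercise and 4 as control. If the data are released under those same numbers, anyone who has read the article knows the arms. Letter codes avoid this, but the section never says that they replace the numbers.

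**4. Contact time** (Study design; 20 sessions per active arm).

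- Combination: 15 + 30 = 45 min per session; 45 x 20 = 900 min
- Stimulation: 30 min per session; 30 x 20 = 600 min
- Exercise: 15 + 30 = 45 min per session; 45 x 20 = 900 min
- Control: 0 min of experimental sessions

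Routine-care contact in the control arm is not quantified and is left out.

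**5. Bang's index.** The article prints no formula. I assume the usual per-arm form, with every respondent in the denominator:

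index = (correct - wrong) / all respondents

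A form centred for four named arms is

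rescaled = (correct - wrong/3) / all respondents

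| Behaviour in an arm | Correct | Wrong | Unsure | Usual index | Rescaled |
|---|---|---|---|---|---|
| All guess among four arms | 0.25 | 0.75 | 0 | -0.50 | 0.25 - 0.25 = 0 |
| All five answers equally likely | 0.20 | 0.60 | 0.20 | -0.40 | 0.20 - 0.20 = 0 |
| Half Unsure, the rest guess | 0.125 | 0.375 | 0.50 | -0.25 | 0.125 - 0.125 = 0 |
| Half name the right arm, none Unsure | 0.50 | 0.50 | 0 | 0 | 0.50 - 0.167 = 0.33 |

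Under guessing, the usual form is negative by an amount that depends on how many answer Unsure. With no Unsure answers, its zero corresponds to 50% correct, twice the 25% expected by chance. The rescaled form is zero in all three guessing rows.

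**The case against.** The strongest reply is that nothing is hidden. The Discussion lists the missing sham first among its limitations, names the expectancy effect, and calls for future work to balance attention and expectation. The Blinding section adds general consent wording that does not reveal which arm is experimental, treatment teams told only their own protocol, separate rooms, and a formal blinding check. Two blinded psychiatrists make the cognitive and symptom ratings. All of this stands, and a reader who inferred concealment would be wrong. But these measures limit what patients expect of their treatment, not what they know they received. The limitation also leaves the Methods and Table 1 making the opposite claim.

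Three stronger readings are tempting and go too far:

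- **That analysts will be fully unblinded.** The article states the intention to withhold identities and also describes letter codes. The arms are revealed only if the numbering from the Randomization section is reused.
- **That unblinding before lock would let data be edited with the arms known.** The first step is described as grouping only. The principal investigator who performs it already assigns the measures to the groups, so its timing tells that person nothing new. The article does say "Access to the securely stored eCRFs will be restricted to the project leader and the principal investigator", but access is not the same as editing rights, and the Auditing section adds a comparison of paper and electronic records every two weeks.
- **That only three codes exist for four arms.** The three letters are given as an example.

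On Bang's index, its adaptation to four arms could properly be left to an analysis plan that is not shown. That is why this limb is secondary. It remains a point because the article claims that the index separates unblinding from guessing, and in its usual form it does not do so with four named arms.

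**Conclusion.** The concern holds as a set of contradictions in the text. The double-blind label and the claim that all participants and researchers are blinded are incompatible with the article's own account of the arms, the missing sham and the researchers' knowledge. The accurate description is assessor- and analyst-blinded, and the analyst part depends on resolving the lock order and the codes.

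The size of any expectancy bias cannot be derived from the document, and none is claimed here. What can be stated is the imbalance in experimental session time: 900, 600, 900 and 0 minutes over the course, assuming full attendance. The Bang's index result rests on the usual formula and on guesses spread evenly over the four arms. Under those assumptions the chance value lies between -0.25 and -0.50 in the cases shown, and it moves towards 0 as Unsure answers increase.

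**What to change.** 1. **Label.** Replace double-blind with randomised, assessor- and analyst-blinded throughout, including the Abstract, Table 1 and the Figure 2 caption. Delete the claim that all participants and researchers are blinded. State that contrasts with control include expectancy and contact-time effects.
2. **Order.** State once that the first unblinding takes place only after database lock.
3. **Codes.** Use one scheme: four randomly assigned letters unrelated to arm numbers 1 to 4, with the key withheld from analysts until the analysis is complete.
4. **Blinding check (secondary).** Use (correct - wrong/3) over all respondents. Alternatively, report the share correct among those who named an arm against 25%, and give the share answering Unsure separately.

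None of this needs a sham arm, more patients or more visits. The cost is wording, a recoded key and one formula, submitted through the route in the Protocol modifications section. Recruitment has begun, but all of it can be in place before lock. The one real price is a less favourable design label.
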